### Outcomes assessments

Assessments will be conducted at baseline (pre-admission clinic), and 6 weeks, 6 months and 12 months after randomisation by assessors blinded to treatment allocation. Demographic information collected at baseline will include height, weight, socioeconomic data (highest level of education completed, health insurance status, employment status, occupation), history of lower limb arthritis and joint surgery and the 19-item Hospital for Special Surgery Knee Replacement Expectations Survey [37,38]. This survey has been tested for internal consistency (Cronbach's alpha = 0.77) and test-retest reliability [37].

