### Health economic outcomes

Participants will prospectively record in a patient diary the following:

• presenteeism (self-reported capacity to work or perform daily activities) [58-60]

• instances of absenteeism

• use of healthcare and community services

• out-of-pocket costs of community services

These data will be collected over three six-week time periods from: (i) discharge from acute care, (ii) the 6-week follow-up assessment, and (iii) the 6-month (26-week) follow-up assessment.

Presenteeism will be rated from 0% (unable to do usual work/activities) to 100% (fully functioning). Absenteeism is defined as days off work (including home, volunteer or carer duties) due to TKR. The use of healthcare (e.g. visits to medical practitioners, physiotherapists, hospitalisation) and community (e.g. meals on wheels) services will be recorded in terms of the type of service, date of use and number of hours/days. Costs of community services will be the out of pocket costs incurred by participants. The use of medication will be included as a health economic outcome and will be collected at the time of each follow-up assessment.

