### Statistical analysis

Statistical analysis will be by intention to treat and coded to ensure blinding to treatment allocation. For continuous data, two-way repeated measures ANOVA incorporating treatment groups at the three follow-up time points (6 weeks, 6 months and 12 months) will be carried out. The significance of any differences in dichotomous data (OMERACT-OARSI treatment responders, proportion of patients reporting sufficient leisure time physical activity, number of adverse events) will be tested using generalised estimating equations or linear mixed model. If there are chance imbalances in baseline patient characteristics hypothesised to influence the main outcomes, then statistical techniques that allow adjustment for confounding variables will be used as secondary analyses. If there are more than 5% missing data, sensitivity analysis allowing for different assumptions such as the best or worst possible scenario will also be reported for the main outcomes of the study.

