### Health economic analysis

The economic evaluation will consist of a trial-based cost-utility analysis to assess the incremental cost per quality-of life-year (QALY) of the novel rehabilitation strategy compared to usual care. The primary analysis will be conducted from the perspective of the health sector. A secondary analysis will entail a societal perspective in which the additional costs (and cost savings) associated with use of community services, absenteeism and presenteeism will be factored in.

In the primary analysis, costs of healthcare services will be valued at standard rates published by the Australian Government: the Medical Benefits Scheme standard fees for medical services and procedures, the Pharmaceutical Benefits Scheme cost for medications and the Australian Refined Diagnosis Related Groups (AR-DRG) cost weights for hospital services. These will be factored with levels of utilisation to estimate the costs of healthcare use in participants.

In the secondary analysis, costs of community services will be based on the self-reported costs of participants. The costs of presenteeism will be estimated by the number of days worked weighted by the rate of presenteeism multiplied by the average wage rate for the relevant employment category. The costs of absenteeism will be estimated by the number of days absent from work multiplied by the average wage rate for the relevant employment category. For those engaged in unpaid work, the national average wage rate will be used. A separate set of cost-utility ratios will be presented in this secondary analysis incorporating the wider costs (and cost savings) to the community.

Health state utilities required to estimate QALY will be based on measures obtained from the SF-12 and transformed into health state utilities via the SF-6D algorithm [62]. Although no survival difference is expected between the two groups at 12 months, average quality of life over 12 months for each participant will be estimated and weighted by survival up to 12 months to determine, for each patient, a measure of QALY after TKR. Given likely variations in the 'usual care' across sites, separate incremental cost-utility ratios will be estimated for broad categories of usual care (inpatient or outpatient). Sensitivity analysis will test uncertainty in key parameters such as the selection of cost weights and statistical variation in quality of life scores.

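### The incremental QALY has no pre-specified estimate adjusted for baseline utility, although the SF-12 is collected before randomisation

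*Protocol article*

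**What the plan says.** The Health economic analysis section gives the source of the utilities: "Health state utilities required to estimate QALY will be based on measures obtained from the SF-12", transformed by the SF-6D algorithm. The next step is described thus: "average quality of life over 12 months for each participant will be estimated and weighted by survival up to 12 months". The stated purpose of that step is "to determine, for each patient, a measure of QALY after TKR". The section does not say how the visits are averaged, whether the pre-operative value enters, or by what model the two groups' QALYs are compared. It neither names nor rules out baseline utility. Its examples of sensitivity analysis are cost weights and variation in quality-of-life scores.

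On timing, the Outcomes assessments section states: "Assessments will be conducted at baseline (pre-admission clinic), and 6 weeks, 6 months and 12 months after randomisation". The SF-12 is among the secondary outcomes, and strength testing is the only measure explicitly restricted to later visits, so a baseline SF-12 will exist. The opening part of Methods places randomisation after surgery and before discharge from the ward, so the baseline value is pre-operative and pre-randomisation. The Health economic outcomes section equates six months with week 26 ("the 6-month (26-week) follow-up assessment").

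On adjustment, the Statistical analysis section models continuous data at the three follow-up visits and does not name baseline as a covariate. Adjustment depends on a condition: "If there are chance imbalances in baseline patient characteristics hypothesised to influence the main outcomes". Where that condition is met, the section provides that "statistical techniques that allow adjustment for confounding variables will be used as secondary analyses". No other adjustment rule appears in the article.

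**The concern.** A participant's utility before surgery is likely to predict utility over the following year, and so the QALY. If QALYs are compared without it, two things follow. The variation that baseline explains stays in the standard error, and whatever baseline difference chance produces passes in part into the incremental QALY.

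The QALY difference is likely to be small, and it is a denominator, so a shift that would be minor in a clinical score can move the cost-utility ratio noticeably. The Discussion places cost-effectiveness in the primary aim and describes the trial as adequately powered for economic benefit.

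The one adjustment rule does not meet the need. Even if it is extended to the QALY, adjustment would depend on looking at the data first and would yield only a secondary result. No reading of the article gives a primary, pre-specified, baseline-adjusted estimate.

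**Working it through.** The article states no QALY difference, utility SD or correlation, so it has no figure of its own to reproduce on this point.

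**Inputs from the article:** total sample 600 and 15% loss to follow-up (Sample size); visits at baseline and at weeks 6, 26 and 52.
**Assumed inputs:** utility SD 0.12 (range 0.10 to 0.15); slope of QALY on baseline utility 0.5; correlation between baseline utility and QALY 0.5 to 0.6.

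1. Participants per arm: 600 × (1 − 0.15) / 2 = 255.

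2. Standard error of the chance baseline difference: SD × √(2/n) = 0.12 × √(2/255) = 0.0106. At SD 0.10 it is 0.0089, and at 0.15 it is 0.0133.

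3. Shift in the unadjusted incremental QALY per standard error of imbalance: 0.5 × 0.0106 = 0.0053.

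4. Scale of that shift. A utility gain of 0.03 at weeks 26 and 52, with none earlier, is worth 0.0208 QALY by time weighting. One standard error of imbalance would turn this into 0.0208 − 0.0053 = 0.0155 or 0.0208 + 0.0053 = 0.0261. With the cost difference held fixed, the ratio would be multiplied by 0.0208/0.0155 = 1.34 or 0.0208/0.0261 = 0.80.

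5. Precision. Adjustment reduces the variance by the squared correlation: 0.5² = 25% to 0.6² = 36%. To match this without adjustment would take 1/0.75 = 1.33 to 1/0.64 = 1.56 times as many participants.

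6. Sensitivity to the averaging rule. Assume equal SDs of 0.12 and the same correlation r between any two visits. The first variant is time-weighted with baseline placed at week 0 (weights 3/52, 13/52, 23/52 and 13/52, that is 0.058, 0.250, 0.442 and 0.250). The second is a plain mean of the three follow-up visits.

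| r | QALY rule | Slope | SE unadjusted | SE adjusted | Variance cut |
|---|---|---|---|---|---|
| 0.3 | time-weighted | 0.34 | 0.0077 | 0.0068 | 22% |
| 0.3 | three follow-ups | 0.30 | 0.0078 | 0.0071 | 17% |
| 0.5 | time-weighted | 0.53 | 0.0086 | 0.0066 | 42% |
| 0.5 | three follow-ups | 0.50 | 0.0087 | 0.0069 | 38% |
| 0.7 | time-weighted | 0.72 | 0.0095 | 0.0057 | 65% |
| 0.7 | three follow-ups | 0.70 | 0.0095 | 0.0059 | 61% |

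The gain from adjustment is similar under either rule. A larger imbalance, of 1.96 standard errors, would shift the time-weighted QALY difference by 0.006 to 0.019 over SD 0.10 to 0.15 and r 0.3 to 0.7.

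7. Averaging, taken separately. For assumed utility differences of 0, −0.02, +0.02 and +0.02 at the four visits, the QALY gain is 0.0088 time-weighted, 0.0067 as a three-visit mean and 0.0050 as a four-visit mean. Without the early loss, the first two are 0.0139 and 0.0133, about 4% apart.

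**The case against.** The strongest reply is that the article is silent on the QALY model, and silence is not a decision to leave baseline utility out. The covariates of an economic regression are often left to a fuller plan, which is not shown here. This stands in part: the article cannot be said to have chosen an unadjusted comparison. But it does state a rule on adjustment, its only one, and that rule is conditional and secondary. That stated rule is what needs changing.

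The second reply is that chance imbalance is not bias, and that a valid unadjusted interval already allows for it. This is correct. A reader might infer that the cost-utility result would be biased; under randomisation it would not be. What remains is avoidable imprecision and a shift conditional on the imbalance that occurs.

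A reader might also infer that the QALY is a plain mean of unequally spaced visits and so wrongly weighted. The text does not support that. An average over 12 months can be time-weighted, and over one year a time-weighted mean equals the area under the curve. In the example above, the methods differ by 0.002 to 0.004, well below the standard error of the QALY difference at the same assumed SD. Nor is a trapezoid that starts at the baseline value clearly right: that value is pre-operative, randomisation follows surgery, and the measure is described as a QALY after TKR. The same timing does no harm to baseline utility as a covariate, since it is measured before randomisation.

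Finally, every magnitude rests on assumed SDs, slopes and correlations. That is so, and the ranges are given for that reason.

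**Conclusion.** The point holds in a limited form. The article gives the incremental QALY no pre-specified baseline-adjusted estimate, although the covariate will have been collected. The cost is efficiency, plus a conditional shift of about 0.005 QALY per standard error of imbalance (SD 0.12, 255 per arm, slope 0.5). The variance saving is about 25% to 36% at a baseline-QALY correlation of 0.5 to 0.6, and 17% to 65% across the wider assumptions in the table. The direction does not depend on the averaging rule; the size depends on quantities that the article does not give. Visit weighting is an ambiguity to clear up and is not a demonstrated error.

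**What to change.** In Health economic analysis, state that the incremental QALY in the primary economic analysis will be estimated by regression on treatment arm, baseline SF-6D utility and the randomisation strata (recruitment site; unilateral or bilateral TKR), whether or not a baseline imbalance is observed. An unadjusted difference can be reported beside it.

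As a clarification, state that the 12-month average is time-weighted over the visits. State also how the interval from randomisation to week 6 is handled, given that the baseline value is pre-operative.

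The cost is a few sentences of analysis wording. No new data, visits or participants are needed.

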## Discussion

The primary aim of the proposed pragmatic randomised controlled trial is to compare the effectiveness and cost-effectiveness of a novel rehabilitation strategy, consisting of an initial home exercise programme followed by higher intensity outpatient exercise classes, to usual rehabilitative care in people undergoing primary TKR for OA. The trial incorporates methodological features that have been shown to reduce bias [63-66]. Participants will be assigned to the novel rehabilitation strategy or usual care by random, concealed allocation with an audit trail. Outcomes assessments will be blinded. The nature of the treatment precludes blinding of the therapist and the participant, but statistical analysis will be blinded to treatment allocation and will be conducted in accordance with 'intention to treat' methods.

Current evidence does not support the usual practice of providing outpatient rehabilitation in the period immediately following discharge from the acute orthopaedic ward after TKR in terms of improving self-reported of physical outcomes. In light of the increasing incidence of TKR, the need to develop clinically effective and cost-effective rehabilitation programs for the growing number of people undergoing TKR surgery is paramount.

The MARKER Study is a pragmatic randomised controlled trial designed with sufficient power to detect meaningful clinical and economic benefits if they exist. The evaluated rehabilitation programme is class-based, utilises only simple and widely available equipment and can therefore be easily implemented in clinical practice. If effective, the novel rehabilitation strategy could optimise outcomes in people after TKR and allow substantial cost savings to both the health sector and more widely across the community when compared to the usual, resource-intensive one to one outpatient intervention. Furthermore, our own observations indicate access to early outpatient rehabilitation is affected by a patient's impaired physical state and driving restrictions. A programme that allows home exercise in the early recovery period followed weeks later by outpatient rehabilitation circumvents this access problem, thus potentially facilitating improved patient adherence to a prescribed supervised programme.

Currently 10 large orthopaedic centres and associated physiotherapy outpatient departments have pledged collaboration. It is anticipated that the MARKER Study will commence patient recruitment in early 2009. The one-year follow-up of all study participants should be completed by the end of 2011.
